#### Economic evaluation

The economic evaluation involves calculating cost-effectiveness and cost-utility ratios. In the pair wise comparison of the mean groups, bootstrapping is used to calculate confidence intervals around the mean difference in costs and ratios. Incremental costs and benefits of the intervention compared to usual care are presented in cost-effectiveness planes and acceptability curves. Substitution of costs is analyzed by describing volumes of healthcare use and associated costs in both groups.

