### Measurements

Table 1 provides an overview of all effect and economic measurements. At baseline (T0), and after 6 (T1) and 12 months (T2) trained interviewers visit participants. At baseline and after 6 months, they leave cost diaries for patients and caregivers to register medical consumption during the successive 6 months. These cost diaries also provide the possibility to visualize delivery of the intervention and usual care. When patients are unable to fill out a questionnaire, their informal caregiver is allowed to fill it out or to provide assistance.

**Table 1 T1:** Measurement Scheme

**variable**	**Instrument**	**T0**	**T1**	**T2**

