**Effect evaluation: secondary outcomes**				
b. Quality of life of the caregiver	SF-36 [48]	X	X	X
	EQ 5-D [57]	X	X	X
c. Psychological well-being of the caregiver	CES-D [49]	X	X	X
d. Caregiver's burden	SPPIC [50]	X	X	X
e. Days until institutionalization of the patient	GP	continuous registration		
f. Quality of life of the patient	DQOL [51]	X	X	X
	EQ 5-D [57]	X	X	X
g. Days until death of the patient	GP	continuous registration		
h. Hospital days of the patient	Cost diaries	continuous registration		

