#### Economic evaluation

The economic evaluation is performed from a societal perspective. The evaluation is a combination of a cost-effectiveness analysis on caregiver's sense of competence (SCQ) and two cost-utility analyses on caregivers and patients separately. Utilities are based on the EQ-5D [57]. Quality Adjusted Life Years (QALY) are calculated by multiplying the utility with the amount of time a patient spends in this particular health state [58]. Incremental costs per QALY gained are calculated. In all analyses, direct costs inside and outside health care are considered. Besides, indirect costs of productivity loss of caregivers and indirect costs of the intervention are estimated. Direct costs inside health care (e.g. costs of consulting the GP, hospitalizations, and use of medication), direct costs outside health care (e.g. costs of traveling, costs of informal care, and costs of consulting alternative health professionals), and productivity loss are assessed by means of cost diaries for caregivers and patients, in which subjects register the amount of healthcare they use. Indirect costs of the intervention, such as nurses' trainings, are calculated using the bottom-up method, by measuring all resources and multiplying these by associated cost prices. Dutch guidelines for economic evaluations in health care are followed to estimate costs [59].

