### Analysis

#### Effect evaluation

Data are primary analyzed according to the intention-to-treat principle. Additionally, data are analyzed according to the on-treatment (i.e. per protocol) principle in order to examine whether protocol deviations have caused bias. General Linear Models are used to analyze differences between the intervention and usual care group on caregiver's sense of competence, caregiver's quality of life and caregiver's psychological well-being. Potential baseline differences are accounted for by covariates. Differences in days until institutionalization and death between patients of the two groups are tested with survival analyses (Cox-proportional hazard modeling). Differences on patient's hospitalization days and patient's quality of life are tested by a chi-square test and student t-test, respectively. Potential confounding is checked, including the effect of different interviewers and nurses.

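### Bootstrap intervals around the two cost-utility ratios are likely to be uninterpretable at this sample size; incremental net benefit should be reported from the same replicates

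*Protocol article*

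**What the plan says.** In the protocol article, the economic part of the Analysis section opens: "The economic evaluation involves calculating cost-effectiveness and cost-utility ratios". It then says that "bootstrapping is used to calculate confidence intervals around the mean difference in costs and ratios". The ratios are one on the SCQ and, from the economic part of the Measurements section, "two cost-utility analyses on caregivers and patients separately". The type of bootstrap interval is not named.

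The next sentence of the Analysis section adds: "Incremental costs and benefits of the intervention compared to usual care are presented in cost-effectiveness planes and acceptability curves".

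On QALYs, the Measurements section says: "Quality Adjusted Life Years (QALY) are calculated by multiplying the utility with the amount of time a patient spends in this particular health state". The visits supply the utilities: "At baseline (T0), and after 6 (T1) and 12 months (T2) trained interviewers visit participants". Table 1 lists the EQ-5D at all three visits for caregiver and patient. The effect-evaluation part of the Analysis section says "Potential baseline differences are accounted for by covariates". The economic part neither repeats this nor rules it out.

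**The concern.** A cost-effectiveness ratio divides a cost difference by an effect difference. If bootstrap effect differences fall on both sides of zero, the ratios no longer have a meaningful order:

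- Cost +1,000 and QALY -0.02 (dominated) gives -50,000. Cost -1,000 and QALY +0.02 (dominant) also gives -50,000.
- Cost +1,000 and QALY +0.02 gives +50,000. So does cost -1,000 and QALY -0.02, which is a different decision.
- As the effect difference passes zero, the ratio runs off to infinity with either sign.

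An interval made by sorting such values can have limits that say nothing about value for money. Cost-effectiveness is one of the article's two main research questions, and its Discussion ties a recommendation to implement to proven effectiveness and cost-effectiveness. The interval on that answer should therefore be readable.

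**Working it through.** **1. Number analysed.** Inputs from the sample size section: SCQ SD 5.2, range 4-27 (width 23), 15% difference, alpha 0.05, power 0.80. The base of the 15% is not stated. Taken on the scale width, it is 0.15 x 23 = 3.45 points. Then n = 2 x (1.96 + 0.84)^2 x 5.2^2 / 3.45^2 = 36 per arm by the normal formula, and 36.65, so 37, by the t-test. This reproduces the stated 37. Dropout: 37 / 0.75 = 49.3, so 50 per arm and 100 in total, as stated.

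**2. SCQ ratio.** SE = 5.2 x sqrt(2/37) = 1.209. If the observed difference equals 3.45, the share of replicates at or below zero is Phi(-3.45/1.209) = Phi(-2.85) = 0.2%. The 95% interval for the effect includes zero when the observed difference is below 1.96 x 1.209 = 2.37. That happens in 19% of trials if the true effect is 3.45, and in 70% if it is half of that (1.725).

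**3. Cost-utility ratios.** The article gives no QALY SD or QALY gain, so both are assumed. SE = SD x sqrt(2/37), and the share of replicates at or below zero is Phi(-gain/SE) when the observed gain equals the assumed one. In brackets is the probability that the 95% interval for the QALY difference includes zero when the assumed gain is the true one.

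| Gain | SD 0.10 | SD 0.15 | SD 0.20 | SD 0.25 |
|---|---|---|---|---|
| 0.02 | 19.5% (86%) | 28.3% (91%) | 33.4% (93%) | 36.5% (94%) |
| 0.03 | 9.8% (75%) | 19.5% (86%) | 25.9% (90%) | 30.3% (92%) |
| 0.05 | 1.6% (42%) | 7.6% (70%) | 14.1% (81%) | 19.5% (86%) |

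Worked cell: 0.20 x sqrt(2/37) = 0.0465, and Phi(-0.02/0.0465) = 33%. If all 50 per arm were analysed, the SE would be 0.20 x sqrt(2/50) = 0.040 and the share Phi(-0.5) = 31%, so dropout is not what drives the result.

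**4. Behaviour of the intervals.** A simulation used 37 per arm, 1,000 trials and 1,000 replicates each. Effects were normal and costs gamma (mean 15,000, SD 10,000), drawn independently. Intervals were percentile intervals, with willingness to pay of 30,000 per QALY or 500 per SCQ point. All of these cost and threshold inputs are assumptions. Net benefit is threshold x effect difference - cost difference. The Monte Carlo SE at 95% coverage is sqrt(0.95 x 0.05/1000) = 0.7 points.

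| True effect, cost difference | True ratio | Ratio coverage | Median ratio-interval width | Net-benefit coverage |
|---|---|---|---|---|
| SCQ 3.45, 1,000 | 290 | 95.8% | 3,853 | 93.5% |
| SCQ 1.0, 1,000 | 1,000 | 98.9% | 38,607 | 95.3% |
| QALY 0.02, 1,000 | 50,000 | 97.6% | 1,200,465 | 94.5% |
| QALY 0.005, 1,000 | 200,000 | 89.1% | 1,186,721 | 94.9% |
| QALY 0.002, 1,000 | 500,000 | 61.1% | 1,192,838 | 94.0% |
| QALY 0.005, 5,000 | 1,000,000 | 58.6% | 2,330,981 | 94.4% |

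**5. Baseline utility.** Assume linear interpolation between the 0, 6 and 12 month visits. The 12-month QALY is then 0.25 u0 + 0.50 u1 + 0.25 u2. If utilities have equal SD at each visit and correlation r with baseline, a baseline difference d carries d x (0.25 + 0.75r) into the QALY difference: a factor of 0.625 at r = 0.5 and 0.775 at r = 0.7. For an assumed utility SD of 0.15, one SE of chance imbalance is 0.15 x sqrt(2/37) = 0.035, which carries 0.022-0.027. For an SD of 0.25 it is 0.058, which carries 0.036-0.045.

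**The case against.** **The defect is conditional.** This stands. A reader might infer that ratio intervals are meaningless throughout. They are not: at the design SCQ effect almost no replicates cross zero and coverage is about 96%. The poor coverage (59-61%) needs true QALY differences of 0.002-0.005. At 0.02 coverage is 98%. What remains at 0.02 is interpretability: the median interval is about 1.2 million wide around a true ratio of 50,000, and its limits can still come from replicates with opposite meanings.

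**The plan already shows the uncertainty in a sound way.** This also stands in large part. The plane shows which quadrants the replicates occupy, and an acceptability curve is the probability that net benefit is positive at each threshold. A decision need not rest on the ratio interval. But the plan still commits to that interval, and the curve gives a probability, not a size with an interval.

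**Percentile ordering is an assumption.** The article does not name the interval type. The quadrant problem affects any interval built by ordering ratios; the coverage figures apply to percentile intervals only.

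**Baseline utility.** A reader might infer that QALYs are to be compared unadjusted and that the comparison is therefore biased. Neither follows. The article is silent, and a pairwise comparison of group means, mentioned where the bootstrap is introduced, does not exclude covariates. An article may leave the QALY model to a fuller plan. Under randomisation the unadjusted difference is unbiased, and chance imbalance is already part of the sampling error that the bootstrap reflects. Adjustment would gain precision only.

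**Conclusion.** The point holds in a limited form. The article fixes bootstrap intervals around ratios in a trial with no powering on QALYs. For the two cost-utility ratios the replicates are likely to span zero: 10-37% at or below it for gains of 0.02-0.03 and SDs of 0.10-0.25, and as little as 1.6% in the most favourable cell examined (gain 0.05, SD 0.10). Where they do, the interval can be uninterpretable and, very near zero, can lose coverage. Net-benefit intervals stayed at about 94-95% in every scenario simulated.

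The sizes depend on assumed QALY and cost inputs, because the article gives none. The SCQ ratio is at risk only if the observed effect falls well below 3.45. The documents do not support discarding the planes and curves, nor calling the QALY comparison biased. The primary SCQ analysis and the sample size are unaffected.

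**What to change.** In the economic part of the Analysis section:

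- Keep the planes and acceptability curves.
- Report each ratio as a point estimate. Give an interval around it only when the replicates do not cross zero on the effect axis. Fix in advance whether this means none at all or a stated negligible share, since even at the design SCQ effect about 0.2% cross.
- Add incremental net benefit with a bootstrap 95% interval, from the same replicates, over a stated range of willingness to pay per QALY and per SCQ point.
- For precision, state that the QALY difference is estimated by regression on arm and T0 EQ-5D utility, and the SCQ difference in the economic analysis by regression on arm and baseline SCQ.

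The cost is a few sentences and modest programming. No new data are needed.

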## Discussion

In this paper we described the study protocol of an innovative RCT that evaluates case-management by district nurses to primary informal caregivers of men and woman aged 65 or over with dementia symptoms who live at home, and the older men and women who receive informal care. This is one of the first trials on case-management that includes an economic evaluation. Moreover, it concerns a tailor-made intervention in early-detected patients with dementia symptoms and their caregivers. In addition, the detection method of patients with dementia symptoms preceding recruitment of these patients and their informal caregivers is unique. A large general practice population of older patients was approached by mailed questionnaires. Particular strengths of our study protocol are the randomization approach, in which allocation concealment involves an external independent person, and methods used to enhance the quality of measurements such as assessors who are blinded to group assignment and training of assessors. Another strength is the possibility to visualize delivery of the intervention and usual care by cost diaries. Cost diaries might also provide insight in factors related to the intervention process that may influence the effectiveness of case-management.

Below, we describe design features that address potential threats to reliability and validity. Firstly, selection of participants may limit generalization of the results of this study as selective non-response of older adults, selective refusal of caregivers, and selective dropout are possible. Non-responding older adults in other studies have been observed to have higher rates of functional and cognitive impairment [61,62]. To limit this potential selection bias we will send personalized invitation letters by GPs and provide reminders to initial non-responders. This strategy has shown to be effective [63]. Furthermore, we anticipate that caregivers check mail of cognitively impaired individuals and provide help with filling out as inhabitants are informed about the project by a newspaper article. Selective refusal of caregivers to participate might be assumed as some caregivers will label cognitive impairment as an accepted aspect of normal ageing, or do not experience adverse consequences of caregiving. Possibly, such caregivers will refuse more often than other caregivers. The same might be assumed about severely burdened caregivers who could be afraid to become even more burdened with participating in the project's measurements. To limit such selective refusal, interviewers will contact potential participating caregivers after screening to inform them about the project before sending personalized invitation letters to them. To prevent selective drop-out of severely burdened caregivers and severely disabled patients, appointments for measurements are made by one fixed interviewer on times and locations suitable for the participants.

Secondly, two situations may cause information bias. Firstly, bias may occur as cognitively impaired subjects without insight may fill out questionnaires. However, as we assume that detected patients suffer mainly from mild or moderate dementia symptoms, and insight is mainly preserved in these subjects, this bias probably will be limited. Secondly, in the economic evaluation, caregivers are allowed to provide assistance or to fill out the EQ-5D when patients are unable to fill out this questionnaire. This may lead to information bias, as it is known that agreement on the EQ-5D between patients and caregivers is poor [64]. However, this bias probably will be limited as well, as we assume that detected patients suffer mainly from mild or moderate dementia symptoms, and most patients will fill out the questionnaire themselves.

Thirdly, contamination could bias results of this study as we choose to perform randomization on patient level. However, influence of contamination on results is unlikely as participants of the usual care group have no access to particular activities of the intervention (e.g. family meetings, RAI-HC assessment, guide for informal caregivers). Nevertheless, it is possible that participating GPs are encouraged by the project to give more attention to patients with dementia symptoms and their informal caregivers participating in the usual care group.

Lastly, we expect heterogeneity in study subjects because response to interventions may be different depending on caregiver circumstances. In combination with the relatively small sample size of approximately 100 participants, this heterogeneity may make it hard to interpret the outcomes. However, increasing the sample size is not feasible. Therefore, we will visualize distribution of characterizes over comparison groups to estimate the influence of this heterogeneity on outcome measures. Moreover, cost diaries will detect heterogeneity in received care within the usual care group as well as in the case-management group.

The results of this RCT will provide valuable information for health professionals and policy makers on effectiveness and cost-effectiveness of timely tailor-made case-management for patients and their informal caregivers. Moreover, positive effects will challenge current health care systems to move to more pro-active approaches for this group. In case of proven effectiveness and cost-effectiveness, we recommend implementing this case-management intervention into usual healthcare. The results of this study will be available in autumn 2006.
